**6.5 Inclusion and inclusion Criteria**

**Inclusion**

- Coupes whose wives are pregnant (1st trimester)
- Couples at least having one live birth
- Couples whose wives are of childbearing age
- Couples who lived in the study area at least six months before the study
- Couples living in the study area until 2 months after giving birth
- Couples whose wives' interpregnancy interval is less than two years
- Couples willing to be visited at home

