**6.17 outcomes of interest and measurement**

**Dependent variables:** experience of intimate partner violence (IPV) in the form of physical, psychological, or sexual violence from the male partner is an independent variable of the study among couples.

**Physical intimate partner violence**: During data collection, pregnant women will be asked six physical intimate partner violence questions: (i) “Slap or throw something at her that could hurt her”, (ii) “Pushed shoved her or pulled her hair”, (iii) “Hit her with his fist or with something else that could hurt her”, and (iv) "Kicked, dragged, or beaten her up." (v) “Attempted to choke or burn her on purpose” and (vi) "threatened to use or actually use a gun, knife, or other weapon against her” (Abramsky et al., 2011) in the last 12 months and during the most recent pregnancy. If the mother responds to one or more of these, dichotomous dependent variables will be created from these questions.

If a pregnant mother answers one or more of these physical intimate partner violence questions, 1=yes (experienced physical intimate partner violence), and otherwise, 0=not experienced physical intimate partner violence.

**Sexual intimate partner violence**: A pregnant woman will be asked for three sexual intimate partner violence questions: whether her husband (i) physically forced her to have sexual intercourse with him when she did not want to”, (ii) “forced her with threats or in any other way to perform sexual acts she did not want,” and (iii) "physically forced to perform any other sexual acts she did not want to” (Abramsky et al., 2011) in the last 12 months and during the most recent pregnancy. If the pregnant mother answers one or more of these sexual intimate partner violence questions, 1=yes (experienced sexual intimate partner violence), and otherwise, 0=no (not experienced any sexual intimate partner violence since the start of this pregnancy).

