**6.24 Data processing and analysis**

**Qualitative Data:** The complete data will be exported to ATLAS Ti. 7.0 for data analysis. The codes will be created initially by independent coders. The codes will be merged after discussion to reach consensus codes. At least two coders will be involved in the coding process and categorization of the codes. These codes will be merged into larger categories and then set into sub-themes. Sub-themes will be reviewed further to develop overarching themes**.** Then the data will be summarized and reported with some important direct quotes.

**Quantitative data:** A complete questionnaire with individual code and specific cluster will be exported from server to SPSS or STATA for analysis. At baseline, descriptive statistics such as proportions, percentages, tables, diagrams, and figures will be used to describe the study population at the intervention and control arms before the intervention starts. The baseline characteristics of the participants and their prior exposure to intimate partner violence will be examined and compared between the intervention and control groups. The chi-square test and independent sample t-test will be used to compare the baseline characteristics for categorical and continuous variables, respectively. After the end-line survey, the proportion of women who experienced intimate partner violence during the trial period will be calculated with a corresponding confidence interval.

We will use the McNemar test to appreciate the differences in outcomes of interest in both intervention and control groups before and after the intervention for categorical data. A paired t-test will be used to compare continues outcome of interest in the intervention and the control groups after and before the intervention. A model of longitudinal data analysis, the GEE (Generalized Estimating Equation), will be used to test the independent effect of the intervention on the outcome of the interest. Data analysis will be performed with an intention-to-treat analysis approach. During the analysis, the effect size, confidence interval, and p-value will be calculated. A model with the smallest Quasi-likelihood under the Independence Model Criterion (QIC) will be used to select the best-fitted model. All tests will be two-sided, and statistical significance will be declared at p < 0.05.

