| 233 | How many quintals of the following legume do the family produced in this year? | | | | | 1.Bean  --------  2.pea  -------- | | | | 3. Lentil  -------  4.Nut  ------- | | | | | | 5. Chick pea  --------  6.grass pea  -----------  7.others,pecify | | | | |  | |
| 234 | How many kilograms of vegetables do the family produced? | | | | | 1.Gomen  2.Carrot  3.Potato | | | | 4. Tomato  5. Cabbage  6. Onion  10. Garlic | | | | | | 7.Beat root  8. Pumpkin  9.Pepper  11.Other specify | | | | |  | |
| 235 | How many kilograms of fruits do the family produced? | | | | | 1.Mango 2.Banana  3.Avocado | | | | 4. Papaya  5. Guava  6.Lemon | | | | | | 7. Other specify- | | | | |  | |
|  | **PART THREE: History of recent pregnancy and delivery** | | | | | | | | | | | | | | | | | | | | | |
| 301 | How many live births have you had? | | Enter number……………………………….. | | | | | | | | | | | | | | | | |  | | |
| 302 | Did you attend ANC for your recent pregnancy from skilled health personnel (nurse, mid-wife, and doctor or health officer)? | | Yes………………………….……………..….1  No……………………………………………..2 | | | | | | | | | | | | | | | | | If ‘**no**’  Skip to  **306** | | |
| 303 | If yes, where did you attend? | | Hospital..............................................................1  Health center…..................................................2  Health post/ clinic..............................................3  Home..................................................................4 | | | | | | | | | | | | | | | | |  | | |
| 304 | How many months pregnant were you when you first received antenatal care for the recent pregnancy? | | Enter the number months/weeks……………… | | | | | | | | | | | | | | | | |  | | |
| 305 | Has your baby’s father attended any antinatal visits with you for the most recent pregnancy? | | Yes……………………………….……………1  No………………….………………………….2 | | | | | | | | | | | | | | | | |  | | |
| 306 | Where did you deliver your recent baby? | | Hospital...........................................................1  Health center……….………………………….2  Health post/clinic……..……………………….3  Home…………….…………………………….4 | | | | | | | | | | | | | | | | |  | | |
| 307 | If it is at hospital or health center or health post/clinic, was the husband/partner present during labor or delivery? | | Yes ….………………………………………...1  No …………………………….………………2 | | | | | | | | | | | | | | | | |  | | |
|  | **PART FOUR: HISTORY OF CURRENT PREGNANCY** | | | | | | | | | | | | | | | | | | |  | | |

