| 708 | When I am confronted with a problem, I can usually find several solutions. | | | | | | 1 | | | | 2 | | | | 3 | | | | 4 |  | | |
| 709 | If I am in trouble, I can usually think of a solution | | | | | | 1 | | | | 2 | | | | 3 | | | | 4 |  | | |
| 710 | I can usually handle whatever comes my way. | | | | | | 1 | | | | 2 | | | | 3 | | | | 4 |  | | |
|  | **PART SEVEN: experience of intimate partner violence in the recent pregnancy(last pregnancy)** | | | | | | | | | | | | | | | | | | | | |  |
| 801 | **Physical** | | | | | | | | | | | | | | | | | | |  | |  |
|  | During recent pregnancy, did your partner: | Slap you or throw something at you Yes No  that could hurt you? ………………………………1 2  Push you, shove you or pull your hair……………..1 2  Hit you with his fist or with something  else that could hurt you?..........................................1 2  Kick you, drag you about or beat you up?...............1 2  Attempt to choke you or burn you on purpose?.......1 2  Threaten to use or actually use a gun,  Knife or other weapon against you? …..…………1 2 | | | | | | | | | | | | | | | | | |  | |  |
| 802 | **Psychological** | Yes No  Say or do something to humiliate  you in front of another person?....................1 2  Threaten to hurt or harm you or  someone you care about? ………………...1 2  Insult you or make you feel bad about yourself?...1 2  Do things to scare or intimidate you  on purpose (e.g., by the way he looked at you,  by yelling and smashing things)?...................1 2 | | | | | | | | | | | | | | | | | |  | |  |
|  | During your most recent pregnancy, did your partner: |  |  |  |  |  |  |  |  |  |  |  |  |  |  |  |  |  |  |  |  |  |
| 803 | **Sexual** |  | | | | | | | | | | | | | | | | | |  | |  |
|  | During your recent pregnancy, did your partner | Yes No  Physically force you to have sexual  intercourse with him when you did not want to?.....1 2  Force you with threats or in any other way  to perform sexual acts you did not want?.............1 2  Physically force you to perform any  other sexual acts you did not want to? …………....1 2 | | | | | | | | | | | | | | | | | |  | |  |
| 804 | If a woman is yes for 801 or 802 or 803, what did you do? | Nothing……………………………………………………..…..1  Reported to him relations…………………………………….....2  Quit relationship……………………………………………...…3 | | | | | | | | | | | | | | | | | | If ‘nothing’ skip to  805 | |  |

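### The violence items refer to the previous pregnancy at baseline and, by the same words, to the index pregnancy at endline, so the before/after tests on IPV compare two different pregnancies; the between-arm endline comparison stands

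*Protocol*

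**What the plan says.** **The instrument.** Annex II, Part Seven (items 801 to 803) carries the heading "experience of intimate partner violence in the recent pregnancy(last pregnancy", and the stem of item 802 reads "During your most recent pregnancy, did your partner". Earlier in the same form, "PART THREE: History of recent pregnancy and delivery" includes the question "Where did you deliver your recent baby". A separate block, "PART FOUR: HISTORY OF CURRENT PREGNANCY", follows (items 401 to 407: intention, antenatal care, danger signs, sex of the previous child). It contains nothing on violence. The Amharic heading of the violence block in Annex VI reads as the pregnancy the woman had before this one.

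**The outcome definition.** Section 6.17 says each type of violence is asked about for the last 12 months and the most recent pregnancy. It codes a negative answer on sexual violence as "not experienced any sexual intimate partner violence since the start of this pregnancy" and uses similar present-pregnancy wording for psychological violence. Section 6.21 also names both recall periods.

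**Timing and analysis.** Section 6.16 says the questionnaires are used at baseline and at completion. Section 6.2 puts baseline at no more than 12 weeks' gestation and endline after 8 months of follow-up; section 6.15.1 puts baseline at 10 to 12 weeks. Section 6.24 (data processing and analysis) states "We will use the McNemar test to appreciate the differences in outcomes of interest in both intervention and control groups before and after the intervention" and adds a longitudinal GEE. Section 6.5 requires at least one live birth and "Couples whose wives' interpregnancy interval is less than two years".

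**The concern.** The primary outcome has one definition in the methods and another in the form that collects it. Every participant has an earlier delivered pregnancy, so every woman can answer items 801 to 803 at baseline about that pregnancy, and nothing in the data would reveal the mismatch.

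The first thing at stake is the set of before/after analyses: change between two pregnancies could be read as change under the education programme. The second is the baseline state of the primary outcome. Only 16 clusters are randomised, and participants are recruited after allocation (section 6.12), so violence at enrolment is a natural check on balance between arms and a natural covariate. If objective 1 (prevalence during pregnancy) is estimated from the baseline survey, it too would describe the earlier pregnancy.

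**Working it through.** No figure in the plan bears directly on this point and the sample size does not depend on it. The check compares wording and dates.

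**1. Which pregnancy does the form mean at baseline?** *Recent* and *most recent* could, taken alone, mean the present pregnancy. Four features of the annexes point the other way:
- Part Three uses *recent* for a pregnancy with a known place of delivery.
- Part Four uses *current* for the index pregnancy.
- The Part Seven heading glosses *recent* as *last*.
- The Amharic heading places the pregnancy before this one.

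The husbands' form (items 301, 303 and 305) likewise uses *recent pregnancy*, *last pregnancy* and *recent baby* for one delivered pregnancy. Items affected: 6 physical + 4 psychological + 3 sexual = 13. (Section 6.17 lists three psychological items, the form four.)

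**2. Which pregnancy do the same words mean at endline?** Assume birth at about 40 weeks and 30.44 days per month.
- 8 months = 8 × 30.44 / 7 = 34.8 weeks.
- Baseline at 10 weeks: 10 + 34.8 = 44.8 weeks, 4.8 weeks after birth.
- Baseline at 12 weeks: 12 + 34.8 = 46.8 weeks, 6.8 weeks after birth.
- Counting instead two months (8.7 weeks) from the last session at 33 to 36 weeks gives 41.7 to 44.7 weeks, 1.7 to 4.7 weeks after birth.

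On either count the woman has delivered, and her last pregnancy is the index pregnancy.

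**3. What would McNemar then pair?** The test uses only women whose two answers differ. The first session is at 13 to 16 weeks.
- *No then yes*: includes a woman first abused in weeks 1 to 12 of the index pregnancy, before any session. She appears as a deterioration.
- *Yes then no*: includes a woman whose abuse ended with the earlier pregnancy, before enrolment. She appears as an improvement.

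Both cells can therefore be filled by events that precede the intervention. A GEE that takes baseline violence as a repeated measure inherits this in its time term.

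**4. How far back can the baseline answer reach?** Taking the interpregnancy interval as birth to conception, 24 months + 9 months of earlier pregnancy + about 2.5 months of the current one = 35.5, or about 36 months. This is an upper bound: it applies only to acts at the very start of the earlier pregnancy in a woman at the limit of the interval.

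**5. Would a current-pregnancy answer serve as the *before* value?** No. It covers at most 12 weeks, against about 40 weeks at endline (40 / 12 = 3.3 times as long). The endline window also contains the baseline window, so apart from reporting error a baseline *yes* cannot become an endline *no*. The improvement cell is empty by construction and a rise is built in for both arms.

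**The case against.** The strongest reply is that a pregnancy-to-pregnancy comparison may be intended. The eligibility rules guarantee an earlier, fairly recent pregnancy, and a complete earlier pregnancy is closer in exposure time to a complete index pregnancy than weeks 1 to 12 are. Section 6.24 also calls the baseline information prior exposure, which violence in an earlier pregnancy validly measures. This has weight: the existing answers are worth keeping. But the protocol never states that rationale, and the coding in 6.17 contradicts it.

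Three stronger readings are tempting and are not supported.
- *That the trial's main comparison fails.* The hypothesis in section 5.2 is between arms, kebeles are randomised, and both arms answer the same form. Violence in weeks 1 to 12 is classified alike in both.
- *That 6.17 defines the baseline value as violence in the present pregnancy.* That coding is not tied to the baseline visit and is not explicit for physical violence. The same section also promises a 12-month recall, which at baseline would include weeks 1 to 12. That the early index pregnancy goes unrecorded follows only if the printed form governs.
- *That the recall is 36 months.* That is the extreme case, not the typical one.

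The endline meaning is also partly inferred. Section 6.21 mentions four types of questionnaire, only a women's and a husbands' form are annexed (each in English and Amharic), the Hadiyisa version is not shown, and revision after the pre-test is allowed. Section 6.16 nevertheless says the questionnaires serve both time points, and no different endline wording is given.

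**Conclusion.** The point holds as a contradiction between the outcome definition (6.17, 6.21) and the instrument (Annexes II and VI), with a definite consequence for the before/after analyses. As printed, the form has neither a current-pregnancy nor a 12-month violence item. The within-arm McNemar test on violence, and any GEE time contrast built on baseline violence, would compare two different pregnancies across all 13 items and should not be read as an intervention effect. The between-arm endline comparison is not invalidated, and no sample-size figure changes.

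The conclusion assumes that the annexed wording is what is fielded, that it is reused at endline as 6.16 says, and that birth is near 40 weeks. It should be corrected before baseline, because early index-pregnancy status cannot be recovered reliably afterwards.

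**What to change.** 1. Reconcile the reference period in 6.17 and 6.21 with Annexes II and VI, including whether a 12-month item is wanted.
2. On the baseline form, add a column to the 13 items asking about the time since the start of the current pregnancy. Name the pregnancy explicitly in the English and Amharic headings and in the endline form.
3. Keep the previous-pregnancy answers as a separate prior-exposure covariate.
4. In 6.24, base the effect on violence on the between-arm endline comparison (cluster-adjusted GEE), with current- and previous-pregnancy violence at baseline as covariates. Drop the within-arm McNemar test on violence as evidence of effect, since neither baseline answer is a like-for-like *before* value.

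The cost is a few extra minutes per woman at a visit already planned, and the loss of the within-arm before/after test for this outcome.

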**Annex III: Structured interviewer admininistrative questionnaire for husbands (English-Version)**

Date of the interview (Eth. Calendar) --------------

Identification of interviewer-----------------

Questionnaire I.D----------------------

Interview kebele----------------------

Interview start time-------------------

Interview end time-------------------

| **PART ONE: Background characteristics** | | | | | | | | |  |
| --- | --- | --- | --- | --- | --- | --- | --- | --- | --- |
| S.No | Questions | | Response | | | | | Skip to |  |
| 101 | What is your age? | | Enter complete age in years---------------- | | | | |  |  |
| 102 | What is your wife’s age? | | Enter complete age in years---------------- | | | | |  |  |
| 103 | What is your place of residence? | | Rural………………………………………….…1  Urban……………………………………………2 | | | | |  |  |
| 104 | How long you have been in marriage? | | Enter complete year/s………………………… | | | | |  |  |
| 105 | What is your religion? | | Protestant.............................................................1  Orthodox..............................................................2  Muslim.................................................................3  Catholic ..............................................................4  Others, specify.....................................................5 | | | | |  |  |
| 106 | What is your wife’s religion? | | Protestant..............................................................1  Orthodox...............................................................2  Muslim.................................................................3  Catholic ...............................................................4  Others, specify.....................................................5 | | | | |  |  |
| 107 | What is your ethnicity? | | Hadiya..................................................................1  Kembata...............................................................2  Silte......................................................................3  Amhara.................................................................4  Others, specify.....................................................5 | | | | |  |  |
| 108 | What is your wife’s ethnicity | | Hadiya..................................................................1  Kembata...............................................................2  Silte......................................................................3  Amhara................................................................4  Others, specify.....................................................5 | | | | |  |  |
| 109 | What is your education level? | | No education.........................................................1  Attended elementary school(1-8).........................2  Attended junior or senior high school(9-12)…….3  Attended college or higher(tertiary)education…..4 | | | | |  |  |
| 110 | What is your wife’s education level? | | No education......................................................1  Attended elementary school(1-8).......................2  Attended junior or senior high school(9-12)…..3  Attended college or higher(tertiary)education...4 | | | | |  |  |
| 111 | What is your occupation? | | Farmer .................................................................1  Government employee.........................................2  Self-employed …………………………….........3  Others, specify......................................................4 | | | | |  |  |
| 112 | What is your wife’s occupation? | | Housewife.............................................................1  Government employee.........................................2  Self-employed …………………………….........3  Others, specify......................................................4 | | | | |  |  |
| 113 | What is your average family monthly income in Birr? | | Birr per month(estimate of the respondent)  ………………………………… | | | | |  |  |
| 114 | How many wives do you have? | | One ……………...……………………...….....1  Two and above……………...…………..........2 | | | | |  |  |
|  | **PART TWO: KNOWLEDGE, ATTITUDE AND CONTROLLING BEHAVIOUR QUESTIONS** | | | | | | |  | |
| 200 | **Knowledge** | | | | | | |  | |
| 201 | Have you heard of Intimate partner violence? | | | Yes----------------------------1  No-----------------------------2 | | | |  | |
| 202 | Media, hospitals, health center are examples of sources of information for intimate partner violence | | | Yes ………………………………….1  No …………………………………..2 | | | | 0 | |
| 203 | IPVp is a serious public health issue | | | Yes ………………………………….1  No …………………………………..2 | | | |  | |
| 204 | Slapping, kicking, dragging, beating, choking, pushing, etc., are examples of IPV | | | Yes…………………………………..1  No …………………………………..2 | | | |  | |
| 205 | Forcing partner to have sex when he/she does not want to is sexual violence | | | Yes………………………………….1  No…………………………………..2 | | | |  | |
| 206 | Forcing partner to do something sexual that he/she finds degrading or humiliating is sexual violence | | | Yes………………………………….1  No………………………..………….2 | | | |  | |
| 207 | Belittling or humiliating a partner in front of other people is psychological violence | | | Yes……………………………….….1  No…………………………………...2 | | | |  | |
| 208 | Restricting a partner from contact with family or friends | | | Yes…………………………….…….1  No…………………………………...2 | | | |  | |
| 209 | Intimate partner violence is human right violation | | | Yes……………………………….….1  No…………………………………...2 | | | |  | |
| 210 | **Attitude** | | | | | | |  | |
|  | In your opinion, is a husband justified in hitting or beating his wife in the following situation?  1---------------Yes  2…………… No | | | | | | |  | |
| 211 | If she goes out without telling him? | Yes…………………………………….….…...1  No…………………………………….…….…2 | | | | | |  | |
| 212 | If she goes out without telling him? | Yes…………………………………….….…...1  No…………………………………….…….…2 | | | | | |  | |
| 213 | If she neglects the children? | Yes…………………………………….….…...1  No…………………………………….…….…2 | | | | | |  | |
| 214 | If she argues with him? | Yes…………………………………….….…...1  No…………………………………….…….…2 | | | | | |  | |
| 215 | If she refuses to have sex with him? | Yes…………………………………….….…...1  No…………………………………….…….…2 | | | | | |  | |
| 216 | **Controlling behavior** | | | | | | |  | |
|  | In your opinion, is the husband is justified in controlling his wife in the following  Situation? | | | | | |  | | |
| 217 | Jealous if she talked with other men | | | | 1 | 2 | |  | |
| 218 | Accused her of unfaithfulness | | | | 1 | 2 | |  |  |
| 219 | Did not permit her to meet her friends | | | | 1 | 2 | |  |  |
| 220 | Tried to limit her contact with family | | | | 1 | 2 | |  |  |
| 221 | insisted on knowing where she is | | | | 1 | 2 | |  |  |
| 222 | did not trust her with money | | | | 1 | 2 | |  |  |
|  | **PART THREE: Male Involvement in maternal health care (MHC)** | | | | | | |  | |
| 301 | Did your wife take ANC during her recent pregnancy at health facility? | Yes………………………………………..…...1  No……………………………………….….…2 | | | | | |  | |
| 302 | How long did it take to reach the nearest health institution? | Time in hour……………………………… | | | | | |  | |
| 303 | Have you ever accompanied her to ANC at least once during her last pregnancy? | Yes…………………………….………..…....1  No……………………………….………....…2 | | | | | |  | |
| 304 | If the answer is No why did you not accompy? (**Do not read the alternatives. More than**  **one response is possible**) | Feeling a women’s duty……………………...1  Lack of time to go………………………….…2  Lack of knowledge…………………….……..3  Social stigma………………………….………4  Shyness/embarrassment……………………....5  Fear of HIV test……………………………....6  Non-invitation………………………….……..7  Other specify……………………………….…8 | | | | | |  | |
| 305 | Where did your wife give birth for the recent baby? | Health center ---------------------------------------1  Hospital ---------------------------------------------2  Clinic-------------------------------------------------3  Home------------------------------------------------4 | | | | | |  | |
| 306 | If health institution (hospital or health center or clinic), were you present during labor or delivery? | Yes -------------------------------------------------1  No --------------------------------------------------2 | | | | | |  | |
| 307 | After your wife gave birth to (NAME) did any nurse, midwife or doctor or health officer check on her health? | Yes --------------------------------------------------1  No ---------------------------------------------------2 | | | | | |  | |
| 308 | If Yes for Q, did you accompany during the check-up? | Yes ---------------------------------------------------1  No----------------------------------------------------2 | | | | | |  | |

